## Abstract

**Introduction:**

Prevalence rates of emotional and behavior problems (EBP) in autistic children and youth are high (40–70%), and often cause severe and chronic impairment. Furthermore, autistic children are also more likely to experience family “social-ecological” adversity compared to neurotypically developing peers, including social isolation, child maltreatment, caregiver mental illness, and socioeconomic risk. These family stressors increase the risk of co-occurring EBP among autistic children and can often impede access to evidence-based care, thus amplifying long-term health inequities for autistic children and their caregivers. In the current autism services landscape, there are few scalable, evidence-based programs that adequately address these needs. The *Family Check-Up (FCU®)* is a brief, strength-based, and tailored family-centered intervention that supports positive parenting and explicitly assesses the social determinants of child and family mental health within an ecological framework. Studies have demonstrated long-term positive child and caregiver outcomes in other populations, but the FCU® has not been evaluated in families of autistic children and youth. Therefore, we aimed to evaluate FCU® implementation within an established, publicly funded Autism Program in Ontario, Canada, with delivery by autism therapists, to demonstrate sustainable effectiveness within real-world settings.

**Methods:**

In this study, we outline the protocol for a hybrid implementation-effectiveness approach with two key components: (1) A parallel-arm randomized controlled trial of *N* = 80 autistic children/youth (ages 6–17 years) and high levels of EBP and their caregivers. Primary and secondary outcomes include child EBP, and caregiver well-being and parenting. (2) A mixed methods implementation study, to describe facilitators and barriers to implementation of the FCU® within an autism service setting.

**Discussion:**

Scalable, ecologically focused family-centered interventions offer promise as key components of a public health framework aimed at reducing mental health inequities among autistic children, youth, and their caregivers. Results of this study will inform further program refinement and scale-up.

## Introduction

1

“*Growing up in Canada is like a race. I do not mind if my children are in a race as long as the race is fair*” –[name] (Dan) R. Offord, Child Psychiatrist, 1934–2004.

Engaged, peaceful and well-supported participation of children and youth with disabilities in the major school, home, and leisure domains of their lives is a fundamental determinant of mental health. It is also cornerstone of equity for any society seeking to “make the race fair” for children who fall behind too often. For all children, including those with disability, this includes recognizing both their unmet needs and the assets they bring to their communities, reducing chronic sources of stress, and ensuring that caregivers (e.g., parents) have the resources they need to support their children’s healthy development and their family’s well-being.

Autistic children and youth who also experience co-occurring emotional and behavior problems (EBP) comprise a group that is at particularly high risk of exclusion from meaningful daily social participation in schools and communities. Autism spectrum disorder (ASD) has an early-onset, highly heritable neurodevelopmental profile characterized by core challenges in social communication as well as rigid, restrictive or repetitive behavior and interests and/or sensory sensitivity with 31–55% experiencing co-occurring intellectual disability (1, 2). Up to 70% struggle with problems such as anxiety, hyperactivity, mood difficulties, and challenging behaviors (3). EBP signal increased risk of chronic impairment that cascades across multiple settings (4, 5) and developmental stages from early childhood to later adulthood for autistic people and their families (6–8).

There is growing evidence that the health and development of autistic children and youth are meaningfully influenced by their “developmental ecology,” i.e., their lived environments, which are in turn influenced by more distal social contexts (e.g., neighborhood cohesion, societal income equality, and social welfare policies) (5, 9–12). Autistic children and their families are also more likely to experience ecological adversity, including caregiver marital strain (6), depression (7), stress (3, 8), child experience of bullying (9), and under-involvement in protective social experiences (e.g., friendships, recreational activities) (10, 11). According to Developmental-Ecological models, the daily interactions, routines, and relationships experienced within their family units are most closely and often reciprocally influential (13, 14). Caregivers (e.g., parents) influence emotional and behavioral adjustment among autistic children, especially during key developmental periods, including transitions to school-aged, adolescence, and young adulthood years (5, 10, 15).

Recent longitudinal studies provide compelling evidence supporting the need to integrate an ecological approach into autism and mental health services. One example includes the Canadian Pathways in ASD Study, which is a longitudinal cohort study following over 400 preschoolers from time of ASD diagnosis to late adolescence. Across multiple separate “Pathways” peer-reviewed publications that have examined this data, family socioeconomic status (SES) and relationships, social supports, caregiver depression, stress, and coping have all been linked to later child EBP (5, 12, 16, 17). Furthermore, researchers found that distinct profiles of child and family risk and protective factors may identify families in need of targeted or more intensive support to prevent or diminish child (and family) mental health and developmental risk. Caregiver stress at time of diagnosis was specifically associated with child EBP, family dysfunction and specific caregiver coping styles, and predicted persistent caregiver stress (16). However, caregiver-reported social supports appeared to be protective. Furthermore, children whose families experienced the greatest degree of adversity (e.g., lowest access to social resources and informal supports, high SES risk, and disengaged caregiver emotional coping style) had significantly more impaired behavioral and adaptive functioning outcomes 2 years later. These caregivers also experienced highest levels of personal distress (18).

Supporting parenting and positive family relationships is thus a promising child mental health prevention and intervention approach. Correspondingly, parenting programs have demonstrated benefits among families of autistic children (19, 20), however, provider training and uptake of such programs is low (21). Furthermore, research in populations of both autistic and non-autistic children indicates that more severe child behavior problems and family-level strain (e.g., caregiver depression, low income) often pose barriers to engagement in, and benefit from, such programs, which are typically offered within group modalities, or without an initial assessment of needs (22–24). In contrast, more flexible, tailored, 1:1 approaches may retain and benefit highest-needs families most strongly (25, 26) and thus, may be an important option within a suite of services aimed at supporting autistic children.

Collectively, evidence from longitudinal research indicates that comprehensive mental health interventions for autistic children and youth should seek to decrease barriers to care, systematically assess known modifiable, contextual risk and protective factors for EBP and engage caregivers in a meaningful way as agents of positive change and mental health support for their child. A strength-based approach is particularly essential given higher than average rates of stress and depression among caregivers of autistic children and the harmful psychiatric history of blaming mothers as “causes” of their child’s autism (27). However, to our knowledge, assessment-driven, tailored, family-centered models that assess and act upon ecological risk and protective factors related to child EBP (e.g., caregiver well-being, social supports, family cohesion, and parenting) have yet to be tested among families of autistic children. Furthermore, this is a lifespan problem: social-ecological disparities commonly persist into adulthood, in ways that include social isolation and underemployment (28, 29). Therefore, engaging families of autistic children and youth as early as possible across childhood and adolescence is essential.

### The Family Check-Up®

1.1

The FCU® (federally registered trademark, University of Oregon) is a brief, evidence-based, trans-diagnostic intervention developed to decrease childhood EBP and related impairment (22) by (1) assessing known ecological (child, family, and contextual) risk and protective factors, (2) engaging caregivers in a strength-based, motivational feedback session and plan to enhance positive parenting and family management skills, and (3) connecting participants to a tailored suite of child and family supports within agencies and communities, which may include a tailored, evidence-based package of parenting sessions [“Everyday Parenting Curriculum (EDP)” (23)]. American and European studies of non-autistic children and youth indicate that the FCU® has robust and sustained benefits for child, youth, and young adult emotional and behavioral well-being and related functioning, caregiver mental health, and family connectedness to services (28–31). However, this intervention has not been evaluated within the context of an Autism Service as delivered by primary autism behavioral service providers.

### Initial feasibility and acceptability work

1.2

The current study builds on an initial mixed methods acceptability study of the FCU® as provided to families of autistic children and youth aged 6–17 years old who provided qualitative input on their experience of the intervention and related research measurement battery. A Master’s-level social worker with extensive mental health and family therapy experience was trained and credentialed by FCU® developers to deliver the model to 19 families of autistic children and youth without co-occurring intellectual disability, referred to the program by mental health or developmental pediatrics providers because of significant emotional and/or behavioral problems (e.g., emotional dysregulation, dysphoria, and aggression). Caregivers found the FCU® to be relevant to their families’ needs, particularly the emphasis on the “whole family” including relationships between caregivers and their mental health, and the opportunity to engage in a shared feedback session with older children and youth. Several participants noted that a strength-based approach to parenting was particularly important—that they had previously often felt that they must be doing things “wrong.” They recommended expanding the program to include families of children and youth with lower levels of language and intellectual capacity and to shorten the research measurement battery. This work demonstrated that the FCU® can be delivered with fidelity by Master’s trained mental health professionals to families of autistic children; however, it is unclear whether it can be feasibly delivered by the class of therapists employed in autism programming in Ontario, who often have undergraduate-level credentials and training in behavioral [e.g., applied behavioral analysis (ABA)], as compared to psychotherapeutic or caregiver training, interventions.

### Study objectives

1.3

The current study was designed by a team of clinicians, researchers, and developmental and mental health service administrators with expertise in autism, EBP, and intervention science. Our primary objective was to obtain preliminary estimates of the effectiveness of the Family Check-Up (FCU®) compared to treatment as usual in an Ontario (Canada) sample of 80 families of autistic children and youth aged 6–17 years old who are registered to receive care within a regional autism service and evaluate the feasibility of implementation within this setting. This work aligned with shifts in an Ontario health policy context calling for increased spending on family and child mental health supports, in response to an expert clinical and community stakeholder report (32).

### Family engagement

1.4

We have engaged a Family Advisory Committee to advise on the conduct of the study. The seven-person committee represents families of autistic children with ASD who have participated in the FCU® feasibility study: they provide feedback on exploratory effectiveness measures and caregiver and youth interview guides, advise on recruitment and referral throughout the trial, and will support interpretation of study results and knowledge translation. Members co-develop terms of reference, meet twice/year and receive a stipend. For the proposed study, in response to caregiver input through the feasibility study and advisory groups, we have: adopted more broad and pragmatic inclusion/exclusion criteria, dropped adaptive functioning measures as research outcomes (too burdensome), included FCU® assessments addressing sibling relationships, screen time and online monitoring (identified by families as important indicators), changed wording of some task instructions and included an annual “booster” FCU® at 12 months. Furthermore, our choice of unblinded caregiver reports of child EBP as primary outcome was validated by feasibility study participants’ reports that brief caregiver-child interaction tasks were very helpful clinical tools but not indicative of the full range of their child’s emotional and behavioral challenges over time (i.e., low ecological validity).

## Methods and analysis

2

### Study design

2.1

The step-wise progression of evidence-based practice from efficacy to effectiveness research, and then to eventual implementation into community practice, has traditionally encompassed a lengthy undertaking that has often resulted in poor intervention effects in real-world settings (24, 25). An implementation science approach seeks to shorten this research-practice gap by considering and evaluating outcomes that genuinely reflect real-world settings and concerns (24, 25). We will employ a Type 1 hybrid implementation-effectiveness approach studying the FCU®. This entails evaluating the program’s effects on the emotional well-being and functioning of autistic children and their caregivers (e.g., parents) as delivered by autism therapists trained in the FCU® model using a proof-of-principle randomized controlled trial (RCT) design, integrated with a mixed methods study focused on concurrently and explicitly evaluating facilitators and barriers to the implementation of the clinical intervention within an autism service setting (33). This design is particularly relevant when there is strong face validity for implementing an intervention in a new setting and/or population, indirect evidence of efficacy (e.g., evidence in other populations), and strong impetus to effect systems-level change.

The current study therefore includes two blended components:

#### Effectiveness

2.1.1

The effectiveness study design is a parallel-group effectiveness randomized controlled trial (RCT) within an Autism Service located within a regional tertiary healthcare center serving a large city and surrounding small-urban and rural areas in Ontario, Canada. A sample of 80 children aged 6–17 years who are functionally speaking (or, “functionally verbal”) with clinically confirmed diagnoses of ASD and high levels of EBP and their families will be enrolled and randomized into either the FCU® or treatment as usual (TAU) with outcome assessments at 0, 3, 6, 9, and 12 months.

We will estimate the effectiveness of participation in the FCU® (+ up to 6 months of optional EDP sessions) vs. Treatment as Usual (TAU) by families of autistic children and youth aged 6–17 years in (a) decreasing child EBP (primary outcome), (b) decreasing caregiver depression, parenting stress, and (c) increasing positive parenting practice. (d) We will describe qualitative and quantitative differences in child and caregiver outcomes and connectedness to child and family services between intervention arms, and between FCU® participants classified as responders vs. non-responders.

Primary and secondary outcomes will be measured at 6 months, with follow-up visits at 9 and 12 months to determine if these effects fade out or are sustained.

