#### 3-month assessment (30 min)

2.3.3

This is a brief visit that involves an interview and questionnaires to measure primary and secondary outcomes. It can take place in the family’s home, clinic, a community location, or over the phone with questionnaire completion through emailed links.

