#### 9-month assessment (30 min)

2.3.5

The 9-month visit involves primary and secondary questionnaire outcomes.

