##### Primary outcome

2.4.2.1

Child emotional dysregulation will be measured using the Aberrant Behavior Checklist (ABC) Irritability subscale (51) and the Home Situations Questionnaire—Autism Spectrum Disorder (HSQ-ASD; parent report; 0, 3, 6, 9, and 12 months) (52).

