##### Secondary outcomes

2.4.2.2

The Clinical Global Impressions Scale, Improvement (CGI-I) (53) (blinded interview; 0, 3, 6, and 12 months) will assess primary caregiver impressions of improvement/worsening of EBP, ranging from complete absence of EBP (1) to “disastrously worse” (7). Children will be classified as “responders” for analytic and descriptive purposes if they demonstrated a 25% decrease on the irritability scale and a CGI-I score of 1 or 2.

Caregiver well-being will be assessed by measuring caregiver depression, caregiver anxiety, and parenting stress (parent self-report; 0, 3, 6, 9, and 12 months) Depression will be measured through the Center for Epidemiological Studies Depression Scale-Revised (CESD-R) (54), a 20-item scale with strong psychometric properties.

Caregiver anxiety will be measured using the brief Generalized Anxiety Disorder-7 (GAD-7) (55); and parenting stress will be assessed using a brief version of the Parenting Daily Hassles (56) and the Autism Parenting Stress Index (57).

Specific parenting behaviors will be measured using the Parenting Young Children (PARYC) (58) and Positive Affect Index (59) (parent self-report; 0, 6, and 12 months). The Parental Monitoring Scale (PMS) (60) will also be administered for older children [parent and youth (11+) self-report; 0, 6, and 12 months).

Parenting self-efficacy and coping will be measured using the Parent Empowerment and Efficacy Measure (PEEM) (61) and the Brief COPE (62) (parent self-report; 0, 6, and 12 months). Caregiver thoughts and feelings about their child, and their relationship with their child, will be audio-recorded and coded by assessors blinded to intervention status, using the Autism-Specific 5-Minute Speech Sample (blinded coders; 0, 6, and 12 months) (63). Observed parenting behavior will be coded by blinded observers using a modified version of the Coder Impressions Inventory (COIMP) (64).

Connectedness to and use of services will be measured at 0, 6, and 12 months using a modified version of the Service Utilization Questionnaire developed for a previous Canadian Family Check-Up study.

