#### Effectiveness—aim #1

2.5.1

Analyses will be conducted following an intent-to-treat approach. Two-wave latent difference score models will be used to evaluate whether participation in the FCU®, compared to TAU, is associated with greater decreases in child EBP (primary outcome) and caregiver depression and parenting stress from baseline to 6 and 12 months post-baseline, and greater increases in positive parenting from baseline to 6 and 12 months post-baseline. A sensitivity power analysis indicates that an *N* = 80 is powered to detect a significant regression coefficient equivalent to Cohen’s *d* = 0.56, α ≤ 0.05 (one-tailed), which is aligned with systematic reviews noting moderate (~*d* = 0.60) effect sizes for parenting programs among caregivers of autistic children (19, 20). A one-tailed test was chosen based on our directional hypotheses and the wealth of evidence supporting the effectiveness of the FCU®. Given that *d* = 0.56 is somewhat larger than that found in previous studies of the FCU® in non-autistic children, we will also conduct two additional sets of analyses. First, we will calculate a Bayes Factor for each analysis to determine whether the pattern of effects are more consistent with the null (the two groups do not differ) or alternative hypotheses (the two groups differ). Second, we will conduct exploratory, descriptive analyses to determine the percentage of participants in each condition defined *a priori* as responders using the ABC and CGI, and describe intervention-, organization and policy-relevant child, family and intervention characteristics in each group.

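### The stated two-wave models do not estimate whether the 6-month effect fades, although the 9- and 12-month visits are there to answer that question

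*Protocol article*

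**What the plan says.** Section 2.1.1 of the protocol article sets the schedule, "with outcome assessments at 0, 3, 6, 9, and 12 months", and gives the late visits a purpose: "with follow-up visits at 9 and 12 months to determine if these effects fade out or are sustained".

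The data for this are collected. The primary outcome section (2.4.2.1) lists "HSQ-ASD; parent report; 0, 3, 6, 9, and 12 months" for the ABC Irritability subscale and the HSQ-ASD. Section 2.3.3 says of month 3: "This is a brief visit that involves an interview and questionnaires to measure primary and secondary outcomes". Section 2.3.5 says: "The 9-month visit involves primary and secondary questionnaire outcomes". Caregiver depression, anxiety and parenting stress follow the same five-wave schedule (2.4.2.2). The parenting questionnaires do not ("parent self-report; 0, 6, and 12 months"), and the CGI-I is not scheduled at month 9.

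Section 2.5.1 fixes the analysis: "Two-wave latent difference score models will be used", for change from baseline to 6 months and from baseline to 12 months. It adds a Bayes factor for each analysis and a descriptive comparison of responder percentages.

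**The concern.** Whether an effect fades or lasts is a question about the difference between two arm effects: the effect at 12 (or 9) months minus the effect at 6 months. A two-wave model contains baseline and one later wave. One such model gives the effect at 6 months and another gives the effect at 12, but neither gives the difference between them or its uncertainty. Month 9, one of the two visits assigned to this question, has no place in either model. The Bayes factor and the responder percentages concern whether the arms differ, not whether the difference changes with time.

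At stake is the durability conclusion. Without an estimate of the change in effect, the natural reading is to compare two separate results. That can suggest fade-out when there is none, and persistence when half the effect has gone.

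**Working it through.** **Inputs from the protocol article.** N = 80 (2.1.3); d = 0.56 and one-tailed α = 0.05 (2.5.1).

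**Assumptions.** 1:1 allocation (40 per arm), 80% power for the stated detectable effect, no dropout, and a correlation ρ between the 6- and 12-month results. The protocol gives none of these. ρ is varied from 0.3 to 0.8, with 0.5–0.7 as the central range. d = 0.40 is an illustrative smaller effect, used because 2.5.1 concedes that 0.56 exceeds what earlier FCU studies in non-autistic children found.

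**Step 1: reproduce the stated figure.** The standard error of a standardised mean difference is √(2/40) = 1/√20 = 0.224. The detectable effect is (1.645 + 0.842) × 0.224 = 0.556. At d = 0.56 the expected z is 0.56 × √20 = 2.504, and power is Φ(2.504 − 1.645) = 0.805 (0.799 by noncentral t). The stated 0.56 therefore matches a single two-group comparison at one time point. It says nothing about power for a change in effect.

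**Step 2: side-by-side reading when the effect is fully sustained.** Let the two z statistics be bivariate normal with equal means d√20 and correlation ρ. Then P(significant at 6, not at 12) = P(significant at 6) − P(both significant).

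| True effect at 6 and 12 | P(sig. at 6) | ρ = 0.5 | ρ = 0.7 |
|---|---|---|---|
| d = 0.56 | 0.805 | 0.805 − 0.694 = 0.111 | 0.805 − 0.719 = 0.086 |
| d = 0.40 | 0.557 | 0.557 − 0.392 = 0.165 | 0.557 − 0.432 = 0.125 |

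Over the wider range of ρ (0.8 to 0.3), the d = 0.56 figure runs from 0.070 to 0.132.

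**Step 3: side-by-side reading when half the effect is lost** (0.56 falling to 0.28). P(both significant) is 0.309, 0.326, 0.334, 0.340 and 0.345 at ρ = 0.3, 0.5, 0.6, 0.7 and 0.8. About a third of trials would look sustained.

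**Step 4: what a direct contrast can deliver.** The 6-to-12-month change has SD √(2(1 − ρ)) in outcome SD units, so the contrast has standard error √(2(1 − ρ))/√20. At ρ = 0.5 this is 1.000/4.472 = 0.224. Two-sided 5%, 40 per arm:

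| ρ | Power, complete loss (0.56 → 0) | Power, half loss (0.56 → 0.28) | Loss detectable with 80% power (SD) |
|---|---|---|---|
| 0.3 | 0.56 | 0.18 | 0.74 |
| 0.5 | 0.71 | 0.24 | 0.63 |
| 0.6 | 0.80 | 0.29 | 0.56 |
| 0.7 | 0.90 | 0.37 | 0.49 |
| 0.8 | 0.98 | 0.51 | 0.40 |

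The contrast is usable for complete loss when ρ is about 0.6 or more, and weak for half loss throughout.

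**The case against.** The strongest reply is that a condensed article is being read too literally. Section 2.5.1 does not say that the models are separate, that months 3 and 9 are excluded, or that paired p-values will decide durability. It does estimate the baseline-to-12-month arm difference, and whether the arms still differ at 12 months is a fair reading of a sustained effect. The Bayes factors lessen reliance on significance verdicts. The trial calls itself proof-of-principle and seeks preliminary estimates. The chance of the misleading pattern at the design effect is modest, and the direct contrast has low power for partial fade-out.

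Much of this stands. That fade-out will be declared from significance at 6 months and non-significance at 12 is something a reader might infer, but the article does not say so. The 12-month effect partly addresses durability. The reply does not remove the mismatch, because the article is not silent on method. It names a model class and two time contrasts, and those cannot carry month 9 or yield the change in effect that 2.1.1 says the visits are for. Low power is a reason to report an interval.

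A reader might also infer that leaving out the 3-month score biases the 6-month estimate, or that this score best predicts who is missing at 6 months. The article gives no dropout rate or mechanism, so neither claim is supported. Nor does the inclusion rule in 3.5 (at least some post-baseline data) conflict with the model: under full-information likelihood, a family without a 6-month score can still contribute baseline data, and a 3-month score can enter as an auxiliary variable. The 3-month score also precedes the period in which fade-out would occur.

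**Conclusion.** The point holds as a mismatch between a stated question and the stated method. The 9-month scores, and also the 3-month scores, have no named use, and no stated analysis estimates the change in the arm effect after month 6. This applies in full to the primary outcome and caregiver well-being. For measures taken at 0, 6 and 12 months, only the missing 12-versus-6 contrast applies.

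In size, a side-by-side reading would wrongly suggest fade-out in roughly one trial in ten at the design effect, somewhat more often at d = 0.40, and would wrongly suggest persistence in about one in three when half the effect is lost. These figures depend on the assumed allocation, correlation and absence of dropout. The 6-month comparison is not shown to be wrong. The change is worth making because a stated purpose of the follow-up otherwise goes unanswered.

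**What to change.** Keep the 6-month arm difference as the primary contrast. For each outcome, fit one longitudinal model over the waves collected, either a multi-wave latent change model (which stays close to the method already named) or a mixed model for repeated measures, with an arm-by-visit term. Use 0, 6 and 12 months for the parenting measures. Prespecify, as a secondary durability estimate, the arm difference at 12 months minus that at 6 months with a 95% confidence interval, and show the month-9 arm difference where it is collected. State that a non-significant durability contrast will not be taken as evidence that the effect is sustained.

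This needs no new visits, measures or participants. The costs are revised analysis wording, a few more covariance parameters to estimate at N = 80, and an interval that will often be too wide to separate partial fade-out from none.
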